## Methods and analysis

### Study design and participants

The overall Smart Parents Study follows a stepped-wedge cluster randomized control design, a pragmatic experimental design wherein randomized clusters (i.e., sites) sequentially transition from control to intervention until all clusters are exposed to the intervention (i.e., SPSHK). Sites (*N* = 25) were randomized into 1 of 5 steps which dictated the order in which they would be trained to trained to deliver SPSHK (Table 1). The study described herein focuses on the parent educators at the PAT affiliate sites and follows a prospective, longitudinal, cohort design. Parent educators will be invited to participate in provider-focused research during their onboarding (Figure 1). To be eligible, parent educators must be certified to deliver PAT, engaged in the Smart Parents Study, and have an active parent caseload. Parent educators who elect not to participate in provider research will still have the opportunity to be trained in SPSHK, invite parents to the Smart Parents Study, and deliver the SPSHK visit to families on their caseload.

**Table 1 tab1:** Provider training schedule.

Step	Year 1											
	Sept	Oct	Nov	Dec	Jan	Feb	Mar	Apr	May	Jun	Jul	Aug
Step 1				X	Y							
Step 2					X	Y						
Step 3						X	Y					
Step 4									X	Y		
Step 5											X	Y

X indicates the month in which parent educators at sites in the corresponding step will complete the T0 baseline assessment. Y indicates the month in which parent educators at sites in the corresponding step will complete SPSHK provider training and the T1 post-training assessment.

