### SPSHK training

All parent educators are onboarded to the Smart Parents Study shortly following site enrollment with a 30-min series of self-paced online video modules covering good clinical practice, CSA as a public health problem, and Smart Parents Study procedures. One month prior to their SPSHK training, parent educators will receive a unique link via email to complete an additional 1.5-h series of online video modules. This content will include an overview of the SPSHK curriculum, recordings of a mock SPSHK visit, and reminders about study procedures. The online modules will also include a live 2-h early interventionists orientation to child maltreatment workshop presented by study partners at the Hugh Lane Wellness Foundation.

Following these self-directed and online training efforts, members of the university-based research team will travel to each PAT site to lead a 4-h in-person SPSHK training. Parent educators will receive their copies of the Provider Guidebook (i.e., curriculum manual) and Parent Handbook. In alignment with social learning theory and best practices in provider training, the research team will explain how to navigate the provider guidebook, model delivery of the curriculum, and allow parent educators the time to practice delivering SPSHK in pairs. After completing all training elements, parent educators will record and submit a mock SPSHK visit conducted with a colleague, friend or family member (i.e., not a family on their caseload) to be reviewed by the university-based research team. The research team provides feedback on fidelity to the parent educator (e.g., effective and accurate presentation of material, constructive feedback to practice scenarios, inclusion of all curriculum components, time management) and once mastery is met, certification. Fidelity will continue to be monitored throughout the study with provider implementation forms and parent satisfaction surveys completed after every delivery of SPSHK. Sites will receive a one-time stipend of $1,000 to cover provider training time.

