### Analytic plan

Given that this line of research is embedded within a larger trial (see Study Design), the sampling frame of providers was pre-determined by the number of parent participants needed to power the broader trial. Our primary modeling approach will use linear mixed-effects regression to fit the outcome ‘self-efficacy’ longitudinally over the five study time points (TP). We will include covariates to adjust for study wave (SW), and random intercepts at the provider- and site-level to account for repeat measurements and any potential clustering:

$$\begin{array}{c} \text{self efficacy}=\beta_{0}+\beta_{1}\times TP_{1}+\beta_{2}\times TP_{2}+\beta_{3}\times TP_{3}\\ +\beta_{4}\times TP_{4}+\sum_{j=1}^{5}\beta_{4+j}SW_{j}+\lambda_{i}+\kappa_{j}, \end{array}$$

where 
i
indexes providers and 
j
 indexes sites; 
$\beta_{1}$
 - 
$\beta_{4}$
 represent the coefficients for the fixed effects for each time point; 
$\beta_{5}$
 - 
$\beta_{9}$
, the fixed effects for study wave; and 
$\lambda_{i}$
 and 
$\kappa_{j}$
 represent the at the provider- and site-level random intercepts. We will report 
$\beta_{1}$
 with 95% confidence intervals as our primary measure of the change in self-efficacy from baseline to TP_1_. The same modeling approach will be fit for the outcome ‘attitudes’.

To test for potential effect modification, we will add interaction terms with each moderator at each timepoint. Moderators will include study wave and provider and site characteristics as specified in Table 2. We anticipate minimal missing demographic information for parent educators. Our primary approach to address occasional skipped survey responses will be to use multiple imputation; as a sensitivity analysis, we will conduct best-case and worst-case single imputation (filling in all low scores and all high scores).

**Table 2 tab2:** Study outcomes.

Variables	Measure
Primary outcomes	
Self-efficacy	Project measure
Attitudes	Project measure
Moderators	
Study wave (i.e., step)	N/A
Demographics	Demographic survey
Experience	Demographic survey
Attitudes on EBP	EBPAS
Site-level characteristics	Organizational leadership survey (ILS; ICS)

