#### Sample size justification

The target sample size of 100 parent educators was determined to address a different research aim. To achieve the sample size of parents needed to power the primary outcome for the Smart Parents Study, we anticipated that we would need to engage about 100 parent educators. With the target sample size for the current study, we will have 80% power to detect an effect size in the range *d* = 0.18–0.25 for the change in either self-efficacy or attitudes pre-post, assuming baseline self-efficacy and a test–retest correlation of 60–80% and a significance threshold of 
α=5%
.

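### Provider and site random intercepts do not cover clustering of change within site, so the interval for β1 and, above all, the site-level and wave moderator tests may be unreliable

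*Protocol article*

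**What the plan says.** The Analytic plan writes out the model. It has fixed effects for four post-baseline timepoints and for study wave, plus "random intercepts at the provider- and site-level to account for repeat measurements and any potential clustering". The coefficient β1, with its 95% interval, is the primary measure of change from T0 to T1. The same model serves both outcomes. For Aim 2, "we will add interaction terms with each moderator at each timepoint". Table 2 lists the moderators as study wave, demographics, experience, EBPAS attitudes, and site characteristics from the leadership survey (ILS, ICS).

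Three of these moderators are constant within a site. ILS and ICS are completed by each site's leadership (Measures, Organizational). Wave is the randomised step: the 25 sites "were randomized into 1 of 5 steps which dictated the order in which they would be trained" (Study design and participants).

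On training, "members of the university-based research team will travel to each PAT site to lead a 4-h in-person SPSHK training" (SPSHK training). The Organizational subsection expects sites to differ in leadership and climate, among other things. Aim 2 sets out to explore whether site characteristics moderate the outcomes (Current study).

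On size, the Sample size justification says "The target sample size of 100 parent educators was determined to address a different research aim" and then "we will have 80% power to detect an effect size in the range" d = "0.18–0.25 for the change in either self-efficacy or attitudes pre-post", assuming "a test–retest correlation of 60–80% and a significance threshold of" 5%.

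**The concern.** A random intercept describes clustering of level: some providers and sites score higher throughout. The primary estimand and the moderator tests concern change. A site intercept adds the same amount at every timepoint and drops out of any difference between timepoints. So do the provider intercept and the wave main effect. What remains in the standard error of β1 is the observation-level residual, as if about 100 change scores were independent.

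That is safe only if providers at one site change no more alike than providers at different sites. The article gives reasons for doubt: in-person training is led at each site, sites differ in leadership and climate, and Aim 2 looks for site differences. For interactions of time with ILS, ICS or wave there are only 25 independent units, yet the stated model tests them against the observation-level residual. At stake are the coverage of the primary interval and, more plainly, false-positive findings that site characteristics or wave modify the effect of training.

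**Working it through.** **Inputs.** From the article: N = 100 providers, J = 25 sites, 5 steps, five timepoints, test–retest correlation r = 0.6 to 0.8, 80% power, α = 5%. Derived: m = 100/25 = 4 providers per site and 25/5 = 5 sites per wave, on average. Assumed: α is two-sided, and the within-site ICC of change, ρ, runs from 0 to 0.20.

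**1. The article's own figure.** For a paired comparison on the baseline-SD scale, d = (1.96 + 0.84) × √(2(1 − r)/N).
- r = 0.6: 2.80 × √(0.8/100) = 0.25
- r = 0.8: 2.80 × √(0.4/100) = 0.18

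This reproduces 0.18–0.25, so the stated power treats the 100 change scores as independent.

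**2. Standard error of β1.** With balanced data the model gives Var(β1) = 2σ²ₑ/N; no intercept variance appears. If change has within-site ICC ρ, the true variance is 1 + (m − 1)ρ = 1 + 3ρ times that when the residual is otherwise right. Coverage of the nominal 95% interval is then 2Φ(1.96/√(1 + 3ρ)) − 1, and the detectable d grows by √(1 + 3ρ).

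| ρ (assumed) | 1 + 3ρ | SE ratio | Coverage | Detectable d |
|---|---|---|---|---|
| 0 | 1.00 | 1.00 | 95.0% | 0.18–0.25 |
| 0.05 | 1.15 | 1.07 | 93.2% | 0.19–0.27 |
| 0.10 | 1.30 | 1.14 | 91.4% | 0.20–0.29 |
| 0.20 | 1.60 | 1.26 | 87.9% | 0.22–0.32 |

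**3. Simulation of the stated model.** 25 sites × 4 providers × 5 timepoints, constant r = 0.7, 3,000 runs per setting, using the closed-form equivalent of the random-intercept fit for balanced data. In each cell, the first figure is for site deviations independent at each timepoint and the second for a site effect that persists over T1–T4.

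| ρ | β1 coverage | Type I error, site moderator × T1 | Type I error, wave × T1 (4 df) |
|---|---|---|---|
| 0 | 94.1 / 94.8% | 5.3 / 4.8% | 5.4 / 5.6% |
| 0.05 | 93.7 / 93.1% | 7.5 / 7.4% | 9.0 / 9.7% |
| 0.10 | 91.6 / 90.4% | 9.1 / 11.4% | 12.1 / 14.9% |
| 0.20 | 87.8 / 85.7% | 12.2 / 14.8% | 23.0 / 26.4% |

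Repeat runs put the wave test at 21–28% for ρ = 0.20. A provider-level moderator that varies within site stayed between 4.5% and 6.5%. A site-level analysis of change brought the β1 and site-moderator errors back to about 4.5–6%. With unequal sites (1 to 9 providers, assumed) and ρ = 0.10, the errors were 11.1% for β1, 10.5% for a site moderator and 20.0% for wave.

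**4. Decaying correlation.** The model pools one residual variance over all five timepoints. T0 is one month before training and T1 immediately after it, whereas T2–T4 are annual. Suppose the T0–T1 correlation is 0.7 and the other nine pairs average 0.55 (assumed). The mean correlation is (0.7 + 9 × 0.55)/10 = 0.565, so the pooled residual is about 1 − 0.565 = 0.435, against the 0.30 that applies to T0–T1. The model SE is then √(0.435/0.30) = 1.20 times too large at ρ = 0, and coverage is 2Φ(1.96 × 1.20) − 1 ≈ 98%. A simulation with later correlations falling from about 0.6 to 0.5 (6,000 runs) gave β1 coverage of 98 / 97 / 95 / 92–93% and site-moderator × T1 error of 2 / 3–4 / 4–5 / 7–9% at ρ = 0 / 0.05 / 0.10 / 0.20. The wave test was not rerun under decay.

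**The case against.** A reader might infer that the intervals are certainly too narrow and that Aim 1 will undercover. The article does not support that. It gives no site variance of change: at ρ = 0 nothing is lost, and at 0.05 the standard error of β1 is only about 7% too small. Decaying correlation, which is plausible over three years of annual follow-up, pushes the T1 contrasts the other way and can offset the loss up to an ICC of about 0.10. Contrasts with later timepoints would be hurt rather than helped.

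Nor does the article establish a large site effect. Training follows a common curriculum led by one university team, and includes self-paced modules, practice in pairs and individually reviewed mock visits. It is not described as a single group session per site. Aim 2 explores moderation without asserting it, and a moderator test is affected only by the site variance left after that moderator is fitted.

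It can also be said that degrees of freedom and robust standard errors belong in an analysis plan that is not shown. That is fair for those details. The random-effects structure, however, is written out in full and is said to deal with clustering of any kind, and for change it does not. All of the above limits the size and direction of the problem; none of it restores the claim.

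**Conclusion.** The structural point stands: the stated model leaves clustering of change within site unmodelled. The size is conditional. Under constant correlation and an assumed ICC of change of 0 to 0.20, coverage for β1 runs from about 95% down to 86–88%. At ICC 0.20 the type I error is about 12–15% for ILS or ICS and 21–28% for wave. Under decaying correlation the T1 contrasts can be conservative instead. The fair description is that the error bars are unreliable, with a direction the article cannot settle.

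The firmest exposure is Aim 2, in the ILS, ICS and wave interactions, where only 25 sites carry the information. Provider-level moderators that vary within site are largely unaffected. It would go too far to say that the primary conclusion on β1 would change: the preliminary study's mean change of 0.6 is quoted without a standard deviation, so it cannot be set against these standard errors.

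**What to change.** - Add a site-level random effect on change, either site-by-time or a site random slope for post-training versus baseline. Let residual variance and correlation differ by timepoint, so that the T0–T1 contrast does not borrow a pooled residual from the annual follow-ups.
- Use Satterthwaite or Kenward–Roger degrees of freedom, or small-sample-corrected cluster-robust standard errors by site. Test the ILS, ICS and wave interactions on site-level degrees of freedom: about 25 − 2 = 23 for one site-level moderator and 25 − 5 = 20 for wave.
- Replace the statement that the intercepts deal with any clustering by one that separates clustering of level from clustering of change.
- Say that d = 0.18–0.25 assumes 100 independent change scores, and show it over a range of ICCs of change (about 0.20–0.29 at an assumed 0.10).

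The cost is small and no new data are needed. The extra site variance may be estimated at zero with about four providers per site, in which case site clustering adds nothing to the fitted standard errors. Where site effects do vary, the interval for β1 becomes modestly wider. Data collection is projected to run to August 2028, so the change can still be specified before the final analysis.

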**Figure 2 fig2:**
[figure not shown]
Theory of change.

The 11-item project measure was designed in a preliminary study with inspiration from Myers and colleagues and will be administered at all timepoints (i.e., T0-T4) (33). The purpose of this measure is to evaluate parent educators’ attitudes and self-efficacy pertaining to foundational concepts underlying the SPSHK curriculum (27). Due to small sample size in the study that this measure was originally developed for, it has not been validated. Pending sample size, we will explore a confirmatory factor analysis for latent constructs ‘attitudes’ and ‘self-efficacy.’ In the current study, ‘attitudes’ is operationally defined as the perceptions parent educators have toward the content and delivery modality of SPSHK (i.e., acceptability), both in general and pertaining to their own delivery of the curriculum. Items ask parent educators to respond to statements like “Discussing sex with parents or other adults goes against my personal beliefs” rated on a 5-point Likert scale from (1) Strongly disagree to (5) Strongly agree. ‘Self-efficacy’ is operationally defined in the current study as the extent to which a parent educator feels confident in their knowledge and skills to deliver SPSHK to families on their caseload. This concept is measured with items such as “I know how to respond if a parent asks me a question about their child’s sexual development” rated on the same 5-point scale. An additional 3 open text response items included with this measure at T0 and T1 timepoints ask participants to share thoughts, concerns, and what excites them about delivering the SPSHK visit.

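### The best-case/worst-case imputation is defined on the score level, but the primary measure is a change, so the check need not bound β1

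*Protocol article*

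**What the plan says.** The Analytic plan of the protocol article states the main method for item non-response: "Our primary approach to address occasional skipped survey responses will be to use multiple imputation". It then adds a stress test as a sensitivity analysis: "we will conduct best-case and worst-case single imputation (filling in all low scores and all high scores"). It does not say whether the fill goes in the same direction at T0 and at the later timepoints.

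The same section reports β1 "with 95% confidence intervals as our primary measure of the change in self-efficacy from baseline to TP_1", and fits the same model to attitudes.

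Both outcomes come from the 11-item project measure (Measures, Provider), which "will be administered at all timepoints (i.e., T0-T4"). Items can therefore be skipped on either side of the change. Items are "rated on a 5-point Likert scale from (1) Strongly disagree to (5) Strongly agree". One of the attitudes items shown there is "Discussing sex with parents or other adults goes against my personal beliefs", for which agreement is the unfavourable answer.

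Loss of whole assessments is handled separately: by the mixed model under missingness at random, and by a refit that drops timepoints with more than 30% attrition.

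**The concern.** A best-case/worst-case analysis is useful because the result under any values of the missing responses must lie between the two scenarios. That holds only if each scenario pushes the estimand itself to an extreme. Here the scenarios are described by score level, while β1 is a difference between two score levels. If one extreme is filled throughout, T0 and T1 move in the same direction and the movement cancels in part or in full.

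This is the only sensitivity check stated for skipped responses. If the two scenarios come out close together, the result would look insensitive to skipped items when that had hardly been tested.

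A second, smaller ambiguity concerns attitudes, one of the two primary outcomes. On raw responses, a low score on the negatively worded item is favourable, whereas on a positively worded item it is unfavourable. Low and high match worst and best only after reverse scoring, which the article does not mention.

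**Working it through.** **The plan's own figure.** The article gives no number for this sensitivity analysis. The nearest figure is the detectable pre-post effect in the Sample size justification, d = 0.18–0.25 (n = 100, 80% power, α = 5%, test–retest correlation 0.6–0.8). The two-sided paired formula d = (1.960 + 0.842)·√(2(1−r)/n) gives 0.177 at r = 0.8 and 0.251 at r = 0.6, so it reproduces. It serves below only as a yardstick.

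**Inputs from the article.** Item scale 1 to 5, a range of 4 points. Illustrative change 0.6, the immediate post-training mean change in the preliminary study cited in the Introduction, taken here as points on the item-mean scale.

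**Assumptions.** T0 mean m0 = 3.5, so T1 mean m1 = 4.1. The outcome is scored as an item mean. Answered items have the same mean as all items. The skip shares p0 (T0) and p1 (T1) are not in the article, so a range is shown.

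**Formula.** With fill value a at T0 and b at T1:

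change = [(1−p1)·m1 + p1·b] − [(1−p0)·m0 + p0·a]

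- Same extreme at both timepoints: a = b = 1 (all low) or a = b = 5 (all high). All high minus all low is 4(p1−p0), a gap of 4|p1−p0|.
- Opposite extremes: worst is a = 5, b = 1; best is a = 1, b = 5. The gap is 4(p0+p1).

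Neither gap depends on m0 or m1.

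**Worked case, 5% skipped at both.**
- All low: (0.95·4.1 + 0.05·1) − (0.95·3.5 + 0.05·1) = 3.945 − 3.375 = 0.57.
- All high: (0.95·4.1 + 0.05·5) − (0.95·3.5 + 0.05·5) = 4.145 − 3.575 = 0.57.
- Worst: 3.945 − 3.575 = 0.37.
- Best: 4.145 − 3.375 = 0.77.

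**Range of skip rates.**

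| p0 (T0) | p1 (T1) | All low | All high | True worst | True best |
|---|---|---|---|---|---|
| 2% | 2% | 0.588 | 0.588 | 0.508 | 0.668 |
| 5% | 5% | 0.57 | 0.57 | 0.37 | 0.77 |
| 10% | 10% | 0.54 | 0.54 | 0.14 | 0.94 |
| 5% | 10% | 0.415 | 0.615 | 0.215 | 0.815 |
| 0% | 10% | 0.29 | 0.69 | 0.29 | 0.69 |
| 5% | 0% | 0.725 | 0.525 | 0.525 | 0.725 |

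With equal rates both scenarios equal (1−p) times the change. With unequal rates they separate partly. With skips at one timepoint only, the uniform fill does give the true bounds. In the last row, where skips are at T0 only, all low gives the larger improvement, so the labels reverse.

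**Check by simulation.** Two timepoints, a random-intercept mixed model, 100 providers and 30 replicates were used. With 10% skipped at both, complete data gave 0.548, all low 0.504 and all high 0.495; the opposite fills gave 0.116 to 0.882. With 10% skipped at T1 only, all low gave 0.263 and all high 0.657, identical to the opposite-direction bounds.

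**Scale.** At equal rates the range missed is ±4p: ±0.08 at 2% and ±0.20 at 5%. If the outcome SD is 0.5 to 1.0 points (assumed), d = 0.18–0.25 is 0.18·0.5 = 0.09 to 0.25·1.0 = 0.25 points, which is of similar size.

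**The case against.** The strongest reply is that the article nowhere says the same extreme is used at every timepoint. The words best case and worst case state an intent, and opposite fills at T0 and T1 would honour it. This stands as far as it goes: the uniform fill is the plain reading of the parenthesis, not an explicit statement. If opposite fills are meant, however, the parenthesis misdescribes them and still needs correcting.

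It can also be said that such detail belongs in an analysis plan that is not shown. The article does not leave the rule open, though. It gives a definition, and that definition does not fit the measure it is meant to test.

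The reply on scope has more force. The rule covers occasional skipped items in returned surveys, multiple imputation remains the main method, and attrition has its own handling. At 2% skipped at both timepoints the missed range is only ±0.08 against a change of 0.6, and 10% fits poorly with skips that are occasional. The sentence may also cover measures taken once, such as the EBPAS and the leadership scales, where filling all low or all high raises no question of direction across time. The point is therefore confined to the project-measure outcomes.

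On item direction, reverse scoring is often left to a scoring manual, and nothing says that raw items will be filled. This is a matter for clarification only.

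A reader might infer that the plan is certain to cancel and will report robustness falsely. The documents do not support that. They fix neither the direction of fill by timepoint nor the skip rates, and exact cancellation needs equal rates at T0 and T1.

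**Conclusion.** The point holds in conditional form. If the wording is followed literally and items are skipped at both T0 and T1, the two scenarios differ by 4|p1−p0|, whereas the true bounds on β1 differ by 4(p0+p1). The check then need not bound β1 and can understate its sensitivity to skipped items. When skips are mainly at T0, its best and worst labels also change places.

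The size depends on skip rates that the article does not give: small at 2%, material at 5% or more at both timepoints, and nil if items are skipped at one timepoint only. The gap formulas need only the 1–5 item-mean scale. The individual values also rest on the assumed T0 mean of 3.5 and change of 0.6.

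The primary multiple-imputation analysis and the treatment of attrition are not affected. This is a defect in a sensitivity analysis that should be corrected; it does not invalidate the main result.

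**What to change.** For the two project-measure outcomes, replace the parenthesis with a definition in terms of the change:

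1. Orient all items so that a high score is favourable, reverse-scoring negatively worded ones before any fill.
2. Best case: skipped items take the least favourable score at T0 and the most favourable at T1–T4.
3. Worst case: skipped items take the most favourable score at T0 and the least favourable at T1–T4.
4. Report β1 with its 95% confidence interval under each scenario, beside the multiple-imputation result.

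The all-low and all-high description can stay for measures taken once. The change takes a sentence or two and a few lines of code, with no new data. Its downside is a wider sensitivity interval: 0.37 to 0.77 instead of a single value of 0.57 in the 5% illustration.

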We will track retention carefully and have implemented strategies to promote parent educator retention in both the provider-focused research as well as the broader Smart Parents Study. These strategies include an incremental incentive structure, regular implementation meetings and newsletters, and Smart Parents Study T-shirts, tote bags, and mugs at study milestones. We will explore the rate and pattern of attrition throughout the study, testing for any significant provider-level factors associated with loss to follow up. Our primary statistical method to address attrition if it arises will be to use the mixed-effects regression model above, which implicitly assumes missingness at random. As a sensitivity analysis, we will also fit a version of the model where timepoints with more than 30% attrition are dropped to understand whether results are robust to possible attrition bias.

Open-ended responses from the project measure will be coded in Excel leveraging a phenomenological approach. Qualitative data from the annual semi-structured interviews will be transcribed, deidentified, coded, and analyzed thematically in Dedoose by ≥2 members of the research team with 10% overlap and goal of 90% interrater reliability (36). The codebook will center study aims and be rooted deductively in alignment with the RE-AIM framework; however, we will also allow for inductive coding based on themes that may arise from participant responses (34, 35, 37). The principal investigator will code an additional 10% of interviews chosen at random evenly spread across participants in each study wave to promote reliability throughout.

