### Limitations

The methods described herein have several limitations worth noting due to the study’s nested structure. First, this study is largely dependent on the design and timeline of the parent-focused Smart Parents Study. For instance, delays in the Smart Parents Study (e.g., parent recruitment targets) may translate to delays in training and assessments for the provider study. Second, the sampling frame of providers is limited to those already engaged in the Smart Parents Study as a result of their PAT site’s voluntary participation, which introduces sampling bias. In addition, the number of PAT sites recruited to participate in the Smart Parents Study was determined based on what was needed to adequately power the parent-focused study, not the nested provider-focused study. Lastly, although providers are assured throughout their involvement that assessment responses are confidential, it should be noted that potential challenges related to providers’ discomfort or lack of familiarity with CSA-related content may have an impact on their initial and continued willingness to participate in the provider research component or the extent to which they share during assessments.

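### The planned attrition check, which refits the model without timepoints that lost more than 30%, cannot show whether results are robust to attrition bias

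*Protocol article*

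**What the plan says.** All of this is in the protocol article.

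- **Model (Analytic plan).** A linear mixed model has a separate coefficient for each follow-up timepoint (β1–β4), study-wave terms, and "random intercepts at the provider- and site-level to account for repeat measurements and any potential clustering". β1 is reported "with 95% confidence intervals as our primary measure of the change in self-efficacy from baseline to TP_1". The same model is used for attitudes.
- **Attrition (Analytic plan).** The main method is that mixed model, "which implicitly assumes missingness at random". The sensitivity analysis is: "we will also fit a version of the model where timepoints with more than 30% attrition are dropped to understand whether results are robust". Its stated purpose is to examine possible attrition bias. The rate, pattern and provider-level predictors of loss will also be explored.
- **Skipped responses (Analytic plan).** Multiple imputation, with best-case and worst-case single imputation as a sensitivity analysis, is stated for occasional skipped survey responses. It is not stated for missed assessments.
- **Missed windows (Experimental procedures).** A provider who misses one assessment is still invited to the next.
- **Aim 1 (Current study).** The aim concerns how attitudes and self-efficacy evolve over the whole study period.
- **Limitations.** Discomfort or unfamiliarity with the content "may have an impact on their initial and continued willingness to participate in the provider research component".

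**The concern.** A sensitivity analysis for attrition should vary the assumption in doubt, namely that providers who were not assessed resemble, given their observed data, those who were. This one varies only the set of timepoints, and the same assumption governs what remains.

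The later years matter most. Whether gains last through T2–T4 is central to Aim 1, and annual follow-up over three years is where loss is likeliest to pass 30%. Providers who are uneasy with the topic may be the ones who stop answering, and unease lies close to what the attitudes items measure. If so, β2–β4 would be too favourable, and the planned check has nothing to set against them. Agreement between the two fits on β1 could then be reported as robustness although it was close to guaranteed beforehand.

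**Working it through.** **1. The plan's own figure.** Sample size justification states "we will have 80% power to detect an effect size in the range *d* = 0.18–0.25", with "a test–retest correlation of 60–80% and a significance threshold of" 5%. For a paired change, d = (1.960 + 0.842) × √(2(1 − r)/n). With n = 100:

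- r = 0.8: 2.802 × √0.004 = 0.177
- r = 0.6: 2.802 × √0.008 = 0.251

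The stated range reproduces and is not affected by this point.

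**2. What the refit does to each coefficient.** Time is categorical, so each timepoint has its own coefficient. Removing a timepoint removes that coefficient; it is not re-estimated under another assumption.

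**3. Why β1 hardly moves.** Suppose every provider has T0 and T1. Under random intercepts, each provider's T1 − T0 difference is free of the provider, site and wave terms and is uncorrelated with that provider's T0 + T1 sum and later scores. β1 is then estimated by the mean of those differences, and later visits add nothing. Dropping T2–T4 leaves the point estimate exactly the same. If some providers miss T1 but return later, their later scores inform their intercepts, so β1 can shift a little. The rule that a missed window does not end participation makes this possible.

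**4. Simulation of the stated model.** The article gives no attrition rates, so all of these inputs are assumptions:

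- 25 sites × 4 providers; site, provider and residual variances 0.1, 0.6 and 0.3 (total SD 1, correlation within provider 0.7).
- True β1 = 0.6 and β2–β4 = 0.5.
- Log-odds of loss rise by 1.5 per SD lower current score; 39–57% missing at T2–T4.
- REML fits, 25 replicates per setting.

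| Missing at T1 | β1, all timepoints | β1, after dropping | Largest difference | Truth |
|---|---|---|---|---|
| 0% | 0.603 | 0.603 | 0.000 | 0.6 |
| about 16% | 0.693 | 0.696 | 0.022 | 0.6 |
| about 26% | 0.735 | 0.742 | 0.033 | 0.6 |

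In the last row, T1 itself passed 30% in 5 of 25 replicates. The reduced fit then had no β1, and the row averages the other 20. There the two fits differed by at most 0.033, while both were about 0.14 too high (0.735 − 0.6 and 0.742 − 0.6).

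With T1 complete, the full model gave β2–β4 = 0.664, 0.642, 0.635 against a true 0.5, an excess of 0.14–0.16. With all three timepoints dropped, the reduced fit had nothing to compare with these values.

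**5. Milder assumptions.** A separate set of simulations used loss of 5/20/35/45% at T1–T4.

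- Slopes of 1–2 per SD (odds ratios e¹ = 2.7 to e² = 7.4): β4 = 0.60–0.67 against 0.50.
- Slopes of 0.25–0.5: β4 = 0.52–0.54 if loss is permanent, 0.55–0.59 if intermittent, with a standard error of about 0.095.
- Mean absolute shift in β1 from dropping timepoints, at slopes of 1–2: 0.0006–0.0009 with permanent loss. With intermittent loss it was 0.003–0.004, with a maximum of about 0.018.

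The size of the bias depends on the assumptions. The near-immobility of β1 appears in every setting.

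**The case against.** Four counter-arguments carry weight.

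- **The refit is an addition.** A reader might infer that the 30% rule would delete the primary result if T1 crossed the threshold. The text does not support that: the refit is fitted as well as the primary model, which keeps all timepoints and reports β1–β4. Only the sensitivity refit would lose β1. T1 is also the least likely timepoint to pass 30%, since it comes immediately after training and about a month after T0, with reminders, a six-week window and payment.
- **The protocol does not state that data are missing not at random.** A reader might take Limitations that way, but it says only that discomfort may affect willingness. Both outcomes are measured at every timepoint, and loss driven by earlier observed scores is missing at random, which the mixed model handles. The overlap between discomfort and outcome is also closer for attitudes than for self-efficacy, which is defined as confidence in knowledge and skills.
- **The simulated bias is assumed, and gains survive it.** Strong slopes give the larger figures. A true gain of 0.50 is about five standard errors (0.50/0.095 = 5.3) from zero, so the simulations show inflation, not a false claim of lasting benefit. The assumed changes match the raw mean changes of 0.6 (immediately) and 0.5 (at 6 months) that the article cites from the preliminary study without an SD. Placing them on an SD scale and extending them to three years is a further assumption.
- **Predictors of attrition will be explored.** This is useful description, but it concerns observed factors and cannot test missing at random.

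None of this rescues the check. That outcome-related loss is uncertain is the reason to have a sensitivity analysis that can respond to it.

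**Conclusion.** The concern holds in this form: the stated attrition sensitivity analysis cannot answer the question it is given. That follows from the text alone, because the refit keeps the missing-at-random assumption and drops coefficients without re-estimating them. β1 is exactly unchanged when T0 and T1 are complete. Otherwise it shifted by at most about 0.03 SD in simulation, against a bias of up to about 0.14 SD under the assumed dropout. The main exposure is β2–β4, and so Aim 1.

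The primary model stands. How large any attrition bias will be cannot be known from the article, and outcome-related dropout is plausible but not established. This should be changed before analysis; it does not undermine the design.

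**What to change.** Keep all timepoints, and replace or supplement the drop-timepoint refit with one delta-adjusted (pattern-mixture) multiple imputation or tipping-point analysis of missed assessments. Impute under missing at random, shift the imputed scores by a range of amounts in the unfavourable direction, refit the same model, and report for each of β1–β4 the shift at which the gain is no longer supported.

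Unlike the refit, this responds to the assumption. If a fraction π is missing at a timepoint and T0 is complete, a shift of δ moves that coefficient by roughly π × δ. For illustration, 0.30 × (−0.5 SD) = −0.15 SD.

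Cost: the imputation code planned for skipped items must be extended to whole missed waves, with providers nested in sites, and the later years will carry a less reassuring range. No new data collection is needed.
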